#### Ethics approval and consent to participate

The study was initially approved by the Institutional Review Board (IRB) of the University of Kentucky on March 3, 2023 (protocol # 83904). Research staff members will obtain written informed consent for all participants meeting inclusion criteria prior to study enrollment. Recruitment for this study began October 1, 2023 and will conclude March 30, 2026.

#### Plans to promote retention and complete follow-up

If a participant chooses to leave the study early, data collected until that point will remain in the study database and may not be removed. The intervention will no longer be provided to participants who are removed from this study, and participants will not be compensated for any sessions completed after being removed.

#### Protocol nonadherence and amendments

Participants will not be removed from the study for nonadherence to the study protocol or for missing data. Protocol amendments will be communicated to funding agencies, trial participants, IRB officials, and trial registries.

### Stakeholders

#### Stakeholders eligibility

Age ≥ 18.

#### Recruitment of stakeholders

This is a purposive sample of stakeholders (e.g., community leaders, older adults with T2D, representatives from Barren River Area Development District (BRADD) organizations [Aging on Aging case worker, Community Action]), who will provide feedback, ensure fidelity, and acceptability of the final evidence-based intervention.

#### Pre-intervention

Prior to the start of the intervention, the research team will obtain informed consent and will conduct up to three stakeholder meetings with the following goals: (1) present the final adapted version of the peer health coaching EBI to identify any possible final adaptations to promote pragmatic implementability; (2) finalize operationalization of RE-AIM dimensions based on shared implementation goals; and (3) identify potential facilitators and barriers that might influence implementation. To achieve the third goal, we will use an interview guide tested in previous applications of PRISM [34] across health systems to analyze PRISM contextual determinants, such as external environment, implementation and sustainability infrastructure, and characteristics of participants of the EBI and of the EBI itself. See S1 Fig for study activities involving stakeholders, peer coaches, and peer participants.

### Peer health coaches

#### Peer health coach eligibility

Coaches will be required to:

have a HbA1c less than 7.5% at time of enrollmentage greater than or equal to 55residence in Appalachia Kentucky.

#### Recruitment of peer health coaches

Potential peer coaches will be invited from community centers and senior citizen centers in BRADD. We will mail out recruitment letters that will explain the study and provide contact information for participants to call if they are interested in participating. The same peer health coaches will be involved in all three waves of participant recruitment.

#### Screening of peer health coaches

In addition to meeting the eligibility criteria listed above, peer health coaches will complete an interview with the PI, where the PI will assess peer coach psychological status using the Wallston General Perceived Competence Scale, Campbell Personal Competence Index, Carkhuff Communication and Discrimination Skills Inventories, and Applied Knowledge Assessment (AKA) Scale [35].

#### Pre-intervention training of peer health coaches

The research team will obtain consent from peer coaches. Each potential peer coach will receive 2–3 hours of training. They will complete structured curriculum modules on working collaboratively with study participants, basics of diabetes including self-care activities, knowledge of diabetes medications, recognizing medical "red flags" (e.g., symptoms of hypoglycemia), navigating the clinic, and assessing community resources. The peer coaches will also have training in informal skills development including active listening, non-judgmental communication, and positive social and emotional support. The co-PIs will determine competence, maturity, emotional stability, and verbal communication skills after overall assessment during the screening interview and training. Only coaches who pass a written and oral examination are included in the study.

### Peer participants

#### Sample size

From a statistical perspective, the goal of this pilot and feasibility study is to obtain precise estimates of outcome variability and preliminary effect sizes for each factor (peer support intervention, contact frequency) that can be used to power a large-scale clinical trial. Empirical work by Whitehead and colleagues [36] provides guidance on sample size requirements for pilot studies to accurately estimate the needed size of future trials. For a main trial that aims for 90% power with a two-sided α = .05, a pilot sample size per arm of 25 would be needed in anticipation of a small standardized effect size (e.g., Cohen’s f = 0.1). This study is interested not only in main effects, but also an interaction between peer support intervention and contact frequency. Given that interactions are notoriously underpowered [37]—and given anticipated participant attrition—the decision was made to recruit 19 participants per condition for a total sample size of 76. With this sample size, the detectable effect size for a between-group difference in the primary outcome is Cohen’s f = 0.33 at 80% power with a two-sided α = .05.

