#### Random assignment of peer participants to intervention condition

Participants will be consented, enrolled and randomized into one of four groups. During the consenting process, it will be explained that participants can withdraw at any time. Participant can be randomized into one of the following groups: (1) self-select mentor, once per week contact; (2) self-select mentor, every two weeks contact; (3) matched with mentor, once per week contact; or (4) matched with mentor, every two weeks contact. For participants who are randomized into a group where they are matched with a peer health coach, matching areas include similarity of life stage (e.g., age), county of residence, and duration of disease diagnosis. However, the primary matching area for this study will be county of residence. This decision was informed by key informants who highlighted that Appalachians’ sense of identity is closely linked with the county in which they reside and that there will be an additional level of trust and comfort (or lack thereof) based on where their peer resides. For participants who are randomized into the group where they are able to self-select their peer coach, they will be provided with profiles of eligible coaches. These profiles will include age, sex, marital status, where they reside (county and town), duration of diabetes diagnosis, current HbA1c, and hobbies. Peer participants will be able to rank their top three coaches. The study team will try to match participants with their preferred coach. However, once a coach has been assigned three peer participants, they will be removed from the pool of coaches to choose from.

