## Discussion

Peer health coaching is an approach that relies on social relationships and has resulted in improved outcomes in participants with T2D. In studies of predominantly low-income and minority populations, peer health coaches have been shown to help improve medication adherence and blood glucose monitoring [55–61]. Peer health coaches are usually individuals who have successfully coped with a similar condition as their peer [28]. In peer health coaching interventions, coaches receive training focused on communication skills, including empathetic listening, helping peers clarify life goals, and problem solving with the aim of having the coach support their peer [62]. For the current study, we have chosen a peer coach EBI that showed an HbA1c reduction of 1.07% among peer participants [63].

We acknowledge the following potential challenges with this proposal. First, we may encounter challenges with recruitment and retainment of older adults in rural communities; however, we involved key stakeholders in the development of this study and have included their recommendations in our recruitment efforts along with previously successful recruitment strategies. Second, we acknowledge that older adults may find the use of REDCap links to complete data collection at baseline, 6 months (end of intervention), and 3- and 6-months post-intervention challenging; however, these potential challenges are integral to the evaluation and implementation of the intervention. Lastly, we recognize the lack of a usual care arm may be considered a weakness of our study design and/or a challenge to the interpretation of our findings. Still, we opted not to have a usual care arm because of the dire circumstances of those diagnosed with T2D living in Appalachia Kentucky (e.g., high prevalence, disease severity, lack of resources). In addition, the goal of this pilot and feasibility study is to identify efficacious components to refine a peer support EBI targeting older adults in rural Appalachia. The factorial design provides the scientific rigor to accomplish this goal without the use of a control or usual care group.

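### The detectable effect of f = 0.33 at 80% power treats all 76 recruited participants as analysed, although 76 was set partly to absorb attrition

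*Protocol article*

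**What the plan says.** All of this is in the Protocol article, Sample size, unless another section is named.

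- The pilot is meant to give estimates of variability and preliminary effect sizes for powering a later trial. From published guidance on pilot studies the section concludes that "a pilot sample size per arm of 25 would be needed".
- It then notes that interactions tend to be underpowered and, "given anticipated participant attrition", settles the number: "the decision was made to recruit 19 participants per condition for a total sample size of 76".
- The next sentence gives the sensitivity: "With this sample size, the detectable effect size for a between-group difference in the primary outcome is Cohen’s f = 0.33 at 80% power". The significance level is 5%, two-sided.
- No attrition rate, evaluable number or correlation is given.
- Analytic plan for aim 1 sets the main outcome as HbA1c at the first post-intervention measurement, which Study measurements and outcomes places at six months.
- The Discussion lists retention of older rural adults among the expected challenges.

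**The concern.** The two sentences use one number in two roles. If 76 includes an allowance for losses, fewer than 76 will have the six-month HbA1c, and the sensitivity should be worked out at that smaller number. If 76 is the number to be analysed, there is no allowance for losses.

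What is at stake is how the results are read. Someone who takes f = 0.33 at 80% power at face value will think that a null main effect excludes somewhat more than it does. The sentence also follows directly on a remark about the interaction without saying which contrast it describes, and the same f means something quite different for an interaction.

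**Working it through.** **Inputs from the document.** N = 76 recruited, 19 per cell, hence 38 per level of each factor; two-sided α = 0.05; power 80%; stated f = 0.33.

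**Assumed input.** Attrition of 10% to 20%, because the document gives no rate.

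**Method.** Noncentral F test with df1 = 1, df2 = N − 4 and noncentrality λ = f²N. In a balanced 2x2 design a main-effect difference equals 2f SD, and an interaction, expressed as a difference in differences, equals 4f SD.

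**Step 1: reproduce the stated figure.** At N = 76 and f = 0.33, λ = 0.33² × 76 = 8.28 and power is 81.0%. The f detectable at exactly 80% power is 0.326, which rounds to 0.33. Two other readings do not reproduce it:

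- a 3-df test across the four groups needs f = 0.389;
- one cell against another (19 v 19) needs f = 0.467.

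The plan's figure is therefore a main-effect contrast with all 76 analysed and treated as independent.

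**Step 2: the same calculation with fewer analysed.**

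| Analysed | Loss | Detectable f at 80% | Difference (2f SD) | Power at f = 0.33 |
|---|---|---|---|---|
| 76 | none | 0.326 | 0.65 | 81.0% |
| 75 | 1 person | 0.328 | 0.66 | 80.5% |
| 74 | 2 people | 0.330 | 0.66 | 79.9% |
| 68.4 | 10% | 0.344 | 0.69 | 77% |
| 60.8 | 20% | 0.366 | 0.73 | 72% |

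The stated figure has room for one loss. With two lost, power at f = 0.33 is fractionally under 80%.

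**Step 3: what the same f means for the interaction.** At f = 0.33 a main effect is 2 × 0.33 = 0.66 SD, and an interaction is 4 × 0.33 = 1.32 SD. At 20% loss the interaction figure is 4 × 0.366 = 1.46 SD.

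**Step 4: what baseline HbA1c could give back.** If the analysis gains precision from baseline as a covariate adjustment would, detectable f is multiplied by √(1 − r²), where r is the correlation between baseline and six months. At 20% loss and r = 0.45: 0.366 × √0.7975 = 0.327. At 10% loss and r = 0.30: 0.344 × √0.91 = 0.328. The document states no r.

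**Step 5: shared coaches.** The intraclass correlation (ICC) for coach is not given; 0.05 is assumed here, at 20% loss.

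- Coaches nested within conditions, three peers each: the design effect is 1 + (3 × 0.8 − 1) × 0.05 = 1.07, the effective N is 60.8/1.07 = 56.8, and f = 0.379. Over ICC 0.01 to 0.10 the range is 0.368 to 0.391.
- Coaches fully crossed with conditions and a coach term in the model: f is about 0.366 × √0.95 = 0.357, lower than under independence.

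The direction thus depends on the structure.

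**The case against.** The strongest reply is that nothing has been miscalculated. The figure is right for N = 76, the study is a pilot whose stated goal is estimation, and effectiveness is left to a later, adequately powered trial. This stands as far as it goes: the fault is in the number put into the calculation. A published sensitivity figure should still be consistent with the sentence before it.

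A second reply is that the planned mixed model uses partial data and baseline HbA1c is collected, so the lost precision may be recovered. Step 4 shows that a moderate correlation would do it. A reader might infer that the trial cannot reach the stated sensitivity, but the documents do not support that. The shortfall is shown only for the plain between-group calculation that the protocol used.

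Three further inferences are tempting and should not be drawn.

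- **That 19 per cell falls short of the 25 per arm quoted.** Each factor level has 38, and two arms of 25 make 50, which 76 still covers after a loss of 26/76 = 34%. The section itself warns that interactions are underpowered, and its f = 0.33 sentence speaks of a between-group difference. It does not claim that the interaction is well served.
- **That clustering by coach pushes the detectable effect clearly higher.** The coach limit is explicit ("once a coach has been assigned three peer participants, they will be removed from the pool of coaches to choose from"), and the same coaches serve all three waves. But participants are randomized individually, and the text allows one coach to have peers in different conditions. The usual design effect applies only if coaches are nested within conditions. Neither the ICC nor the number of coaches is given.
- **That f = 0.33 is nearly the whole effect of the source intervention.** The Discussion reports a reduction of 1.07 percentage points for it, but a comparison needs an HbA1c SD, and the document states none.

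**Conclusion.** The point holds in a limited form. The stated f = 0.33 at 80% power is correct for 76 analysed, independent participants in a main-effect contrast, and is inconsistent with the attrition that helped to set 76. On the protocol's own calculation, a loss of 10% to 20% raises the detectable f to 0.34 to 0.37 and lowers power at f = 0.33 to 77% to 72%.

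That loss range is an assumption. The claim that almost any loss takes power below 80% does not depend on it, since two participants suffice. A baseline correlation could offset the loss, and coach sharing could move the figure either way; the document fixes neither. The consequence is modest for a pilot, but the sentence should be corrected.

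**What to change.** Keep 76 recruited and rewrite the end of the Sample size section so that it:

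1. states the assumed attrition rate;
2. gives the detectable effect at the evaluable number, for example about 61 analysed at 20% loss, with a detectable main effect of f about 0.37 (0.73 SD) at 80% power;
3. says that this refers to a main effect, with 38 recruited per factor level, and that for the interaction the same f is a difference in differences of 4f SD (about 1.5 SD at 20% loss);
4. states the assumed correlation with baseline HbA1c, if that is relied on to recover precision;
5. says whether coaches are nested in or crossed with conditions, and shows any effect of coach sharing only as a sensitivity range over stated ICC values.

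This changes one paragraph and adds no participants. The downside is a slightly less favourable stated figure. Keeping 76 evaluable instead would need 76/0.9, or 85 recruited, at 10% loss and 76/0.8 = 95 at 20%. An estimation pilot does not need that.

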### Peer participant eligibility criteria

Eligibility criteria for peer participants include:

confirmed diagnosis of T2D via point-of-care HbA1c assessment;residence in Appalachia Kentucky;HbA1c ≥ 7.5% in the previous 6 months;age ≥ 55 years.

#### Recruitment of peer participants

Peer participants will be recruited from community-based organizations located in the BRADD. Recruitment and enrollment will occur in 3 waves. Within each wave, each coach will be assigned all of their peer participants at one time to ensure that intervention activities occur within the same time period.

#### Screening of peer participants

All individuals who are determined to be eligible for the study will then be screened for cognitive impairment using the Montreal Cognitive Assessment-Basic (MoCA-B) [38] to ensure that study participants have the capacity to engage in study activities.

#### Random assignment of peer participants to intervention condition

Participants will be consented, enrolled and randomized into one of four groups. During the consenting process, it will be explained that participants can withdraw at any time. Participant can be randomized into one of the following groups: (1) self-select mentor, once per week contact; (2) self-select mentor, every two weeks contact; (3) matched with mentor, once per week contact; or (4) matched with mentor, every two weeks contact. For participants who are randomized into a group where they are matched with a peer health coach, matching areas include similarity of life stage (e.g., age), county of residence, and duration of disease diagnosis. However, the primary matching area for this study will be county of residence. This decision was informed by key informants who highlighted that Appalachians’ sense of identity is closely linked with the county in which they reside and that there will be an additional level of trust and comfort (or lack thereof) based on where their peer resides. For participants who are randomized into the group where they are able to self-select their peer coach, they will be provided with profiles of eligible coaches. These profiles will include age, sex, marital status, where they reside (county and town), duration of diabetes diagnosis, current HbA1c, and hobbies. Peer participants will be able to rank their top three coaches. The study team will try to match participants with their preferred coach. However, once a coach has been assigned three peer participants, they will be removed from the pool of coaches to choose from.

### Introductory session for peer coaches and participants

Peer participants and coaches will attend an introductory session together, during which the coaching process will be discussed, including time commitment, roles, responsibilities, benefits, and ground rules. At that time, peer participants who are randomized to self-select their coaches will have the opportunity to review peer coach profiles and rank their top three coaches to be matched. Once coaches and peers have been selected, the quads (coach with three peers) will have the opportunity to ask questions and make informed decisions about their ability to fully participate in the intervention. If face-to-face meetings are not possible for all members of the “quad,” phone or a form of video meeting will be attempted. At this time, the research coordinator will collect demographics, validated questionnaires, and baseline point-of-care clinical outcomes (HbA1c via fingerstick). This introductory meeting as well as the peer coach-peer participant meetings during the six months of intervention can be in-person in community settings or via Zoom, depending upon participants/coach preference.

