### Study measurements and outcomes

Stakeholder’s data will be collected via semi-structured interviews pre-intervention, mid-intervention and post-intervention. Survey data will also be collected from stakeholders’ post-intervention. Peer coaches and peer participants will provide HbA1C levels via blood draw. Peer coaches will complete blood draws and questionnaire data at baseline and end of intervention across all three waves, whereas peer participants will complete blood draws and questionnaire data at baseline, end of intervention (6 months), 9 months and 12 months (see Table 1).

**Table 1 pone.0300196.t001:** Data collection measure instruments.

Measure	Method

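### Baseline questionnaires and the designated baseline HbA1c are collected after randomization, with the coach-selection arm known, so self-reported baselines may react to allocation

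*Protocol article*

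**What the plan says.** The order comes from two consecutive parts of the Protocol article. Under *Random assignment of peer participants to intervention condition*: "Participants will be consented, enrolled and randomized into one of four groups". Under *Introductory session for peer coaches and participants*, the session comes after that step, because it refers to people already allocated: "At that time, peer participants who are randomized to self-select their coaches will have the opportunity to review peer coach profiles". The text continues: "Once coaches and peers have been selected, the quads (coach with three peers) will have the opportunity to ask questions and make informed decisions" on whether they can take a full part. The baseline is then described: "At this time, the research coordinator will collect demographics, validated questionnaires, and baseline point-of-care clinical outcomes (HbA1c via fingerstick").

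No other section places this collection before randomization. The only earlier HbA1c information is in *Peer participant eligibility criteria*, which asks for "confirmed diagnosis of T2D via point-of-care HbA1c assessment" and "HbA1c ≥ 7.5% in the previous 6 months". Neither is named as the study baseline.

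Table 1 lists the questionnaires under primary outcomes, whereas the first study aim calls self-care and psychosocial factors secondary. *Analytic plan for aim 1* names HbA1c at the first post-intervention occasion as the main outcome. It fits mixed models with measurement occasion, peer support type and contact frequency, starting from all two-way interactions.

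**The concern.** One of the two randomized factors is whether the participant chooses a coach or is given one. Several questionnaires measure things that this could move at once: perceived social support, diabetes distress, self-efficacy, depression and quality of life. A participant who has just been offered, or not offered, a choice may answer differently for that reason alone. A baseline that differs between arms because of allocation is no longer a common starting point, and any contrast that subtracts it or adjusts for it carries the difference forward.

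The analysis plan also expects no covariate differences because of randomization and would adjust if some appear. That reasoning holds only for variables that allocation cannot affect. Adjusting for a self-report that has already reacted to the arm can itself introduce bias.

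The decision to take part is made at the same session, after allocation. Someone who dislikes the assigned condition, or does not get a preferred coach because coaches are capped at three participants, may leave before anything is recorded. Such losses need not be equal across arms.

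The *Sample size* section gives the purpose of the pilot as estimating variability and preliminary effect sizes for a larger trial, so a bias in these contrasts would be carried into that planning.

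**Working it through.** **Order of events.** Setting the sections side by side gives:

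1. Consent, enrolment and randomization.
2. Introductory session: those allocated to self-selection review profiles and rank coaches.
3. Same session: groups of one coach and three participants form, and members consider whether they can take part.
4. Same session: demographics, questionnaires and fingerstick HbA1c.

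Step 4 after step 1 is clear. Step 4 after steps 2 and 3 is the natural reading, but the opening words of the baseline sentence could refer to the session as a whole.

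**Bias in a self-reported scale.** Let b be the allocation-caused difference in mean baseline between self-selected and matched participants, in SD units. Let ρ be the correlation between baseline and follow-up. Assume equal SDs at both occasions and a follow-up value unaffected by when the baseline was taken.

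- Change from baseline: true difference minus b, so the bias is −b.
- Baseline-adjusted: true difference minus ρ × b, so the bias is −ρb.

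The article gives neither b nor ρ. Over assumed ranges the absolute bias in SD is:

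| b | Change score | Adjusted, ρ = 0.3 | Adjusted, ρ = 0.5 | Adjusted, ρ = 0.7 |
|---|---|---|---|---|
| 0.1 | 0.10 | 0.03 | 0.05 | 0.07 |
| 0.2 | 0.20 | 0.06 | 0.10 | 0.14 |
| 0.3 | 0.30 | 0.09 | 0.15 | 0.21 |

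If baseline is one of the modelled occasions, the occasion-by-support-type contrast against baseline is a change contrast and takes the full −b. If that interaction is dropped as non-significant, the shifted baseline is averaged into the main effect instead.

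**Loss before collection.** The plan's own figure first. With N = 76, a 1-df factor effect, four cells (72 error df), two-sided α = 0.05 and noncentrality f² × N, the detectable f at 80% power is 0.326. Power at f = 0.33 is 81.0%. The stated 0.33 is reproduced, and the order of procedures does not change it.

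The article anticipates attrition but gives no rate. If the share below were never measured at all (assumed):

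| Loss | N | Detectable f | Power at f = 0.33 |
|---|---|---|---|
| 5% | 72 | 0.335 | 78.8% |
| 10% | 68 | 0.345 | 76.4% |
| 20% | 61 | 0.365 | 71.7% |

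These rows show lost precision only. They do not show the bias that would arise if the loss differed by arm.

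**The case against.** Several stronger readings are tempting, and the article does not support them.

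- **That the baseline HbA1c value is contaminated.** HbA1c reflects glycaemia over weeks, so learning an arm or meeting a coach at the same session cannot materially move it. The main outcome is therefore not biased by this route. The remaining risk for HbA1c is selective missingness.
- **That people who decline at the session have no data and leave the model.** An eligibility HbA1c exists, although it may be up to six months old and is not designated as baseline. *Protocol nonadherence and amendments* says participants are not removed for nonadherence or missing data. Three later measurements are scheduled, and the mixed model uses anyone measured at some occasions. Only full withdrawal removes a person, and an earlier baseline would not then supply the missing 6-month HbA1c.
- **That the bias equals most of the effect the plan anticipates.** The f = 0.1 in *Sample size* (2 × 0.1 = 0.2 SD) is an example used to size a pilot for a future main trial. This study's detectable effect is f = 0.33 (2 × 0.33 = 0.66 SD), stated for the primary outcome. Neither is a yardstick for the questionnaires, so the size is given here in SD units only.
- **That remote attendance makes baseline HbA1c missing or measured differently.** Meetings "can be in-person in community settings or via Zoom, depending upon participants/coach preference", but how a sample is then obtained is operational detail that an article may leave out.
- **That two HbA1c methods are planned.** *Study measurements and outcomes* says "Peer coaches and peer participants will provide HbA1C levels via blood draw", while Table 1 and other sections say point-of-care or fingerstick. This is loose wording, unrelated to baseline timing.

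Two further objections have weight. Participants in every arm meet a coach, so that effect is largely shared, and only the difference between a chosen and a matched coach can bias the selection contrast. Also, the article shows explicitly only that the coach-selection arm is known at the session. It offers no comparable mechanism for contact frequency.

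What stands against all of this is the order itself: the self-reported baselines are taken after randomization, at a session where participants act on their arm.

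**Conclusion.** The point holds for the self-reported baselines and, as a missing-data matter, for participants who leave before collection. The article places baseline after randomization with the coach-selection arm known. An assumed differential shift of 0.1 to 0.3 SD gives a bias of the same size in a change-from-baseline contrast, and about 0.03 to 0.21 SD in a baseline-adjusted one (ρ from 0.3 to 0.7). Whether any shift occurs cannot be told from the article. Those who leave before collection lack a study baseline and questionnaires, and this loss may depend on arm. The order should be changed because the remedy is cheap, and because Table 1 lists the affected scales among the primary outcomes. It does not undermine the HbA1c analysis.

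**What to change.** Collect the baseline questionnaires and the designated point-of-care HbA1c after consent and before randomization. If that cannot be arranged, collect them at least before the arm is disclosed and before coaches are ranked or introduced. State this order in the two sections concerned, and account for every randomized participant in the analysis, including those who leave at or before the introductory session.

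The cost is a longer pre-randomization contact, or possibly an added one, since nine questionnaires plus covariates would move. No new measurement is needed, and eligibility and cognitive screening already require some contact before allocation. Recruitment began on October 1, 2023 and runs in three waves, so a change now may leave baseline timing different between waves. Record the timing for each participant and adjust for wave.
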